## Abstract

**Background:**

Fresh frozen plasma (FFP) is an effective therapy to correct for a deficiency of multiple coagulation factors during bleeding. In past years, use of FFP has increased, in particular in patients on the Intensive Care Unit (ICU), and has expanded to include prophylactic use in patients with a coagulopathy prior to undergoing an invasive procedure. Retrospective studies suggest that prophylactic use of FFP does not prevent bleeding, but carries the risk of transfusion-related morbidity. However, up to 50% of FFP is administered to non-bleeding ICU patients. With the aim to investigate whether prophylactic FFP transfusions to critically ill patients can be safely omitted, a multi-center randomized clinical trial is conducted in ICU patients with a coagulopathy undergoing an invasive procedure.

**Methods:**

A non-inferiority, prospective, multicenter randomized open-label, blinded end point evaluation (PROBE) trial. In the intervention group, a prophylactic transfusion of FFP prior to an invasive procedure is omitted compared to transfusion of a fixed dose of 12 ml/kg in the control group. Primary outcome measure is relevant bleeding. Secondary outcome measures are minor bleeding, correction of International Normalized Ratio, onset of acute lung injury, length of ventilation days and length of Intensive Care Unit stay.

**Discussion:**

The Transfusion of Fresh Frozen Plasma in non-bleeding ICU patients (TOPIC) trial is the first multi-center randomized controlled trial powered to investigate whether it is safe to withhold FFP transfusion to coagulopathic critically ill patients undergoing an invasive procedure.

**Trial Registration:**

Trial registration: Dutch Trial Register NTR2262 and ClinicalTrials.gov: NCT01143909

## Background

Fresh frozen plasma (FFP) is an effective therapy to correct for a deficiency of multiple coagulation factors [1]. International guidelines support its use in case of bleeding in patients with such a deficiency [2,3]. Use of FFP has grown steadily in the past years, in particular in the Intensive Care Unit (ICU) [4]. In the last decade, use of FFP has expanded to include prophylactic administration of FFP. However, there are concerns about the efficacy of FFP to prevent bleeding. Evidence from randomized controlled trials that support FFP transfusion to correct coagulopathy before an invasive procedure is limited, including commonly performed procedures on the ICU, such as insertion of a central venous catheter, a chest drain or a percutaneous tracheotomy [5]. Moreover, retrospective studies suggest that the risk of bleeding after an invasive procedure is low and relevant bleeding requiring blood transfusion or an intervention is less then 1% [6].

Prophylactic FFP may not further reduce bleeding incidence, but carries the risk of acute lung injury, occurring in up to 30% of transfused ICU patients [7], resulting in an increased duration of mechanical ventilation and ICU stay [8,9]. However, despite the absence of evidence, in our ICU patients, 33% of plasma is transfused to non-bleeding patients [10], which is in accordance with reports on ICU transfusion practice in Europe and the United States [11,12].

With the aim to investigate whether prophylactic FFP transfusions to critically ill patients can be safely omitted, a multi-center randomized clinical trial is conducted in ICU patients with a coagulopathy undergoing an invasive procedure.

## Methods/Design

### Objectives and design

The primary objective of the 'Transfusion of fresh frozen Plasma In non-bleeding Critically ill' trial ('TOPIC' trial) is to assess whether omitting prophylactic FFP transfusion is non-inferior to prophylactic FFP transfusion (current practice) to prevent relevant bleeding in ICU patients with a coagulopathy, who are undergoing an invasive procedure.

The preferred design to demonstrate the non-inferiority of no FFP transfusion prior to an invasive procedure against FFP transfusion to prevent bleeding would be a double blind, placebo-controlled clinical trial. However, manufacturing a completely matched placebo in full compliance with the current Good Manufacturing Practice standards was not considered possible for this non-commercial, academic study. Therefore, we have chosen for a multicentre prospective, randomized, open-label, blinded end point evaluation (PROBE) design.

The Institutional Review Board of the Academic Medical Center - University of Amsterdam, Amsterdam, The Netherlands, approved the trial. The TOPIC trial is conducted in accordance with the Declaration of Helsinki and was registered on March 26 2010 at http://www.trialregister.nl with trial identification number NTR2262 and on June 14 2010 at http://www.clinicaltrials.gov with trial identification number NCT01143909.

### Consort Diagram

Figure 1 shows the CONSORT diagram of the TOPIC trial.

**Figure 1 F1:**
[figure not shown]
**CONSORT diagram**.

### Study population

The source population consists of patients admitted to medical-surgical ICUs, who have a prolonged International Normalized Ratio (INR) and will undergo an invasive procedure. Based on previous reports, we expect that 30% of ICU patients have a prolonged INR [13]. A total of 400 patients will be randomized to omitting FFP or receiving 12 ml/kg FFP before a scheduled intervention. Local investigators will screen consecutive patients with a prolonged INR, which is determined daily in all ICU patients. Patients with an INR ≥ 1.5 and ≤ 3.0, who are 18 years and older and will be undergoing an invasive procedure, are eligible. Defined invasive procedures are insertion of a central venous catheter, thoracocentesis, percutaneous tracheotomy or drainage of abscess or fluid collection.

Patients with clinically overt bleeding, e.g. with decrease of hemoglobin > 1 mmol/L, needing transfusion or hemodynamic instability due to bleeding at the time of the procedure or with a thrombocytopenia of < 30 × 10^9^/L are excluded from participation. Also, patients are excluded if they are treated with vitamin K antagonists, activated protein C, abciximab, tirofiban, ticlopidine, low molecular weight heparin (therapeutic dosage), heparin or prothrombin complex concentrates. In addition, patients with a history of congenital or acquired coagulation factor deficiency or bleeding diathesis are excluded. Patients will only be included after informed consent from the patient, his/her (legal) representative or the closest relative has been obtained.

### Randomization and intervention

Patients are randomly assigned to receive or not to receive a single dose of 12 ml/kg FFP. The randomization procedure is password protected, web-based, using permuted blocks and stratified by study centre and invasive procedure. Patients can only be randomized once (e.g. for one procedure). The units of FFP will be ordered from Sanquin, the Dutch National Bloodbank. The chosen amount of 12 ml/kg will lead to an estimated reduction of INR to 1.4 - 1.6.

### Standard procedures

The predetermined invasive procedures are placement of any central venous catheter, percutaneous tracheostomy, thoracocentesis and percutaneous drainage of any fluid collection or abscess. Clinical practices, such as using ultrasound guidance when inserting a central venous catheter, are applied according to each centers specific expertise and routine, to minimize interference of the trial intervention with normal clinical practice.

### Protocol drop out

Subjects can leave the study at any time for any reason if they wish to do so without any consequences. The investigator can decide to withdraw a subject from the study for urgent medical reasons. In patients who develop an acute reaction (increase in body temperature of more than 2°C, hypotension, bronchospasm or development of urticaria), the transfusion will be stopped immediately and adequate clinical measures will be taken accordingly With an incidence of transfusion reaction of 0.1- 1% [3], we expect little drop-outs. Unless patients declare that collected data need to be discarded, data of dropped out participants will be included in the intention to treat analysis.

### Rescue therapy

FFPs will be ordered (but not thawed) from the blood transfusion laboratory also for the patients randomized to the arm with no transfusion. When a relevant bleeding occurs during or after the procedure, these blood products will be readily at hand to be administered.

### Study end points

The primary outcome of this study will be a procedure-related relevant bleeding, occurring within 24 hours after the procedure. Relevant bleeding is defined using a validated tool (HEME) in the critically ill [14]: overt bleeding with any of the following: a decrease in hemoglobin by more then 2 g/dL (1.2 mmol/L) in the absence of another cause or transfusion of 2 or more units red cells without an increase in hemoglobin or a decrease in systolic blood pressure by more then 20 mmHg, or an increase in heart rate by 20 beats per minute or more, or bleeding at a insertion or wound site requiring an intervention. Interventions to cease bleeding are defined as an extra suture at the insertion site, embolization by an intervention radiologist or any surgical intervention required to stop the bleeding. The primary end point will be assessed by a physician who is blinded for the randomization result at 1 and 24 hours after the intervention.

Secondary endpoints include the occurrence of minor bleeding (e.g. prolonged bleeding at the insertion site or increase in size of subcutaneous hematoma), the development of ALI and circulatory overload. For this purpose the Lung Injury Score will be calculated at 24 hours. This score includes chest radiographic score, hypoxemia score (PaO2/FiO2), positive end expiratory pressure (PEEP) level (cm H_2_O), and respiratory system compliance score when available [15]. According to the definition, circulatory overload can be defined as bilateral edema on chest x-ray and a wedge pressure > 18 mmHg. In patients who will not have a SwanGanz catheter in place, circulatory overload will be defined as pulmonary edema in the presence of at least 3 of the following: positive fluid balance, elevated central venous pressure, a history of heart failure and increase in oxygenation in response to diuretics. Furthermore, the effect of FFP on correction of INR and clotting variables and the effect of FFP transfusion on outcome (duration of mechanical ventilation, length of ICU stay and ICU mortality) will be evaluated.

Other variables that are collected include demographics, co-morbidities, severity of illness (Sequential Organ Failure Assessment (SOFA) and Acute Physiology And Chronic Health Evaluation IV, APACHE IV [16]), medication use, hemodynamic and respiratory data (from the electronic patient data monitoring system). Blood samples will be drawn to determine coagulation variables, hemoglobin, blood gas analysis and liver- and renal function.

After the invasive procedure has been completed, repeated assessments will be made after 1 and 24 hours. These will include registration of hemodynamic and respiratory data from the Patient Data Management System (PDMS), a limited physical examination (inspection of the insertion site of the catheter or drain), inspection of drain production, and collection of a blood sample to perform blood gas analysis and assess hemoglobin levels. The limited physical examination will be done by an independent physician blinded for the randomization group. A chest radiograph will be performed 24 hours after the procedure.

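### FFP given to stop a procedural bleed that meets no other criterion is left out of the primary endpoint, a possible bias towards non-inferiority of unknown size that a pre-specified sensitivity analysis should address

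*Protocol article*

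**What the plan says.** The primary outcome is a "procedure-related relevant bleeding, occurring within 24 hours after the procedure". Study end points in the protocol article builds it from overt bleeding plus any one of several criteria:

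- a haemoglobin fall: "overt bleeding with any of the following: a decrease in hemoglobin by more then 2 g/dL (1.2 mmol/L) in the absence of another cause";
- red cells: "transfusion of 2 or more units red cells without an increase in hemoglobin";
- a systolic pressure fall of more than 20 mmHg;
- a heart-rate rise: "or an increase in heart rate by 20 beats per minute or more";
- a site bleed that needs treatment: "bleeding at a insertion or wound site requiring an intervention".

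The last criterion is then closed by a definition: "Interventions to cease bleeding are defined as an extra suture at the insertion site, embolization by an intervention radiologist or any surgical intervention". Plasma is not on that list, and the transfusion criterion does not mention it.

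Rescue therapy states: "FFPs will be ordered (but not thawed) from the blood transfusion laboratory also for the patients randomized to the arm with no transfusion". It continues: "When a relevant bleeding occurs during or after the procedure, these blood products will be readily at hand to be administered". Objectives and design makes the trial open-label with a blinded endpoint assessor.

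Background and Statistical considerations describe relevant bleeding more broadly, as bleeding that needs blood transfusion or an intervention (the latter section adds shock). Neither limits the transfusion to red cells. The assumed 1% event rate rests on that description.

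**The concern.** The trial asks whether FFP can be safely withheld. A patient in the no-FFP arm who is then given FFP because the procedure site bleeds is, on a natural reading, a patient in whom withholding did not work. Unless another criterion is met, the primary endpoint records that patient as free of relevant bleeding.

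The product that goes uncounted is the randomized treatment, and it is given by staff who know the allocation. If it stops bleeds that would have gone on to qualify, and does so more often in the arm that has not yet had FFP, events are lost from the experimental arm. In a non-inferiority comparison that is the anti-conservative direction. With about 2 events expected per arm (198 × 0.01), a small loss matters.

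**Working it through.** **Which bleeds are affected.** Take a patient with an overt procedural bleed who is given FFP.

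| Course | Primary event? | Effect |
|---|---|---|
| A criterion is met before FFP | Yes | None |
| FFP first, a criterion is met later within 24 hours | Yes | None |
| FFP given, no criterion met, none would have been met without it | No | No event lost under the definition, but the use of FFP is not seen by the primary endpoint |
| FFP given, no criterion met, one would have been met without it | No | Event lost |

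Only the last row biases the primary comparison.

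**Inputs from Statistical considerations.** 198 per arm; control rate 0.01; expected difference 0; margin 0.03; one-sided level 0.05; pooled Z test with continuity correction. One input is not in the documents: the share f of true no-FFP events masked by FFP. It is an assumption and is varied below.

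**Step 1: reproduce the plan's figure.** Without continuity correction, n₀ = 2 × 0.01 × 0.99 × (1.645 + 0.842)² / 0.03² = 136.0. With the Fleiss correction, n = (n₀/4) × [1 + √(1 + 4/(n₀ × 0.03))]² = 197.04, which rounds up to the stated 198. Enumerating all binomial outcomes at 198 per arm gives 80.1% power at 1% versus 1%. At 4% versus 1%, the margin itself, non-inferiority is falsely declared in 4.0% of trials. The plan's figure stands.

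**Step 2: how few events decide.** Z = (p_E − p_C − 0.03 + 1/198) / √(2p̄(1 − p̄)/198), and non-inferiority is declared when Z ≤ −1.645.

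- With 2 control and 3 no-FFP events: p_E − p_C = 0.00505, p̄ = 5/396 = 0.01263, standard error 0.01122, Z = −1.77. The trial succeeds.
- With 2 control and 4 no-FFP events: Z = −1.21. The trial fails.
- In general, at most 2 no-FFP events are allowed with 0-1 control events, and at most 3 with 2-3 control events.

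**Step 3: effect of masking.** True rates are 4% and 1%; the recorded no-FFP rate is 0.04 × (1 − f).

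| f (assumed) | Recorded no-FFP rate | False non-inferiority, masking in no-FFP arm only | Same share masked in both arms |
|---|---|---|---|
| 0 | 4.0% | 4.0% | 4.0% |
| 10% | 3.6% | 6.7% | 6.0% |
| 25% | 3.0% | 13.7% | 11.1% |
| 50% | 2.0% | 38.8% | 29.6% |

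For scale, 198 × 0.04 = 7.9 true events are expected in the no-FFP arm, so one masked bleed is about 13% and two about 25%.

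**Step 4: what counting FFP could cost.** If counting it raised the recorded no-FFP rate from 1% to 2% (about 2 more patients in 198) with the control rate at 1%, the chance of meeting the margin would fall from 80.1% to 38.8%.

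**The case against.** A reader might infer that any procedural bleed stopped with FFP drops out of the endpoint, and that the result must therefore lean towards non-inferiority. The documents do not support that. One criterion is enough, so a bleed with the haemoglobin, red-cell, pressure or heart-rate change, or with a listed intervention, is an event whatever stops it. Rescue therapy uses the endpoint's own term as the occasion for rescue, so rescue given as written follows an event. Assessment at 1 and 24 hours does not erase a pressure fall or suture that has already been recorded.

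Further points on that side are fair. The rescue units are not thawed in advance, which makes very early use less likely. The Discussion concedes that pressure and heart-rate changes can occur without bleeding, so over-counting is the weakness the protocol acknowledges. Bleeds below every threshold fit the secondary outcome of minor bleeding. The Discussion ties the same 0.1-0.8% range to red-cell transfusion, so the broader wording in Statistical considerations may be loose rather than intended. That a single event can decide the result is true of any trial with so few events.

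Some of the concern remains. Rescue therapy says when the products will be at hand; it does not say that the endpoint criteria must first be confirmed. The Discussion reports that 30-50% of FFP units go to non-bleeding patients and that ICU physicians assume FFP prevents bleeding, so use for a bleed that does not yet qualify is plausible. Minor bleeding is a secondary outcome with no stated margin. The per-protocol analysis does not restore uncounted bleeds. A sensitivity analysis may sit in an analysis plan that is not shown, but the endpoint definition and its disagreement with other sections are in this document.

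**Conclusion.** The point holds in a limited form. FFP given for an overt procedure-related bleed that meets no other criterion is uncounted, and the protocol article is not consistent on whether transfusion other than red cells makes a bleed relevant. Bias towards non-inferiority is possible but not shown: it needs FFP to be given before a criterion is met, for a bleed that would otherwise have qualified.

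The documents give no rate for that, so its size is unknown. The rise in false non-inferiority from 4.0% to 6.7-13.7% illustrates an assumed masked share of 10-25% in the no-FFP arm, at true rates of 4% versus 1% and with the stated test. If the same share is lost in both arms, which nothing in the documents rules out, the range is 6.0-11.1%. The sample size calculation itself is correct.

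**What to change.** 1. Reconcile Rescue therapy, Study end points and Statistical considerations (with the matching description in Background) on whether plasma given for procedural bleeding counts towards relevant bleeding. Align the time wording as well: Rescue therapy speaks of bleeding during or after the procedure, the endpoint of bleeding after it.
2. Keep the HEME-based primary endpoint.
3. Record, in both arms, FFP or any other haemostatic product given for overt procedure-related bleeding within 24 hours, with its reason.
4. Pre-specify a sensitivity analysis that counts such use as an event in either arm, reported against the 0.03 margin beside the primary result.

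The rescue policy is unchanged.

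The cost is a few sentences and one data item, since the article's list of collected variables does not name FFP given for bleeding. The drawback is that the decision to give FFP is unblinded, so a lower threshold in the no-FFP arm could add events there. That error is conservative for non-inferiority, but Step 4 shows how much power it could take. The analysis should therefore be supportive and not a second success criterion.

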### Statistical analysis

Baseline assessments and outcome parameters will be summarized using simple descriptive statistics. Variables will be expressed by their mean and standard deviation if normally distributed, if not normally distributed they will be expressed by their medians and interquartile ranges. The main analysis focuses on a comparison between the trial treatment groups of the primary outcome, the occurrence of relevant bleedings (using a binary variable), expressed in a relative risk estimate and absolute risk increase. In case of clinically relevant baseline imbalances, the primary outcome will be additionally analyzed using multivariate Poisson or logistic regression, when appropriate.

Secondary outcome parameters such as coagulation variables, acute lung injury, number of ventilation days and length of ICU stay will be expressed using continuous variables. Minor bleedings, occurrence of acute lung injury and serious adverse events will be expressed as binary variables (any versus none). The secondary outcome parameters will be analyzed using the Chi-square test (including RR estimates), two group t-test or Mann-Whitney test, when appropriate. In all analyses statistical uncertainties will be expressed in 95% confidence limits.

Because of the non-inferiority design of the trial, both an intention to treat analysis as well as a per-protocol analysis will be done.

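### New acute lung injury is read from a Lung Injury Score stated only at 24 hours, so lung injury already present at randomisation counts in both arms and attenuates this secondary comparison

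*Protocol article*

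**What the plan says.** The Methods paragraph of the abstract lists "onset of acute lung injury" among the secondary outcomes. The section on study end points speaks of "the development of ALI and circulatory overload" and then gives the measurement: "For this purpose the Lung Injury Score will be calculated at 24 hours". On its components it says "This score includes chest radiographic score, hypoxemia score (PaO2/FiO2), positive end expiratory pressure (PEEP) level", with compliance added when available.

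The same section schedules one film: "A chest radiograph will be performed 24 hours after the procedure". It lists respiratory data and blood gas analysis among the variables collected, without a baseline time point and without linking them to ALI, and then says that "repeated assessments will be made after 1 and 24 hours".

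Under statistical analysis, ALI appears twice: among the outcomes treated as continuous, and as "occurrence of acute lung injury and serious adverse events will be expressed as binary variables (any versus none". Secondary outcomes are compared by chi-square test, t-test or Mann-Whitney test, with no baseline term. The exclusions under study population concern bleeding, low platelets, certain drugs and coagulation disorders; existing ALI is not among them.

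**The concern.** Onset and development are words for a change since baseline. A score taken once after treatment, split into any versus none, measures a state. The two agree only if nobody has ALI at randomisation, and the article neither excludes such patients nor states how they are set aside. The eligible population is critically ill, and duration of mechanical ventilation is itself an outcome, so some lung injury at entry is foreseeable.

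Patients who already have ALI carry little information about whether plasma causes it. Counting them adds the same number of events, on average, to each arm. That shrinks the risk difference, pulls the relative risk toward 1 and widens the interval. The Discussion cites plasma as a risk factor for newly arising ALI and closes by saying that the trial also evaluates plasma's possible harms. A null ALI result from a diluted comparison could be read as reassurance that the design cannot give.

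**Working it through.** **The plan's own figure.** The article states no power or sample size for ALI. Its only calculation is for bleeding: control risk 0.01, true difference 0, margin 0.03, one-sided 5%, 80% power. Without continuity correction, n = (1.645 + 0.842)² × 2 × 0.01 × 0.99 / 0.03² = 136.02. With it, (136.02/4) × [1 + √(1 + 4/(136.02 × 0.03))]² = 197.04, which rounds up to the stated 198 per arm. That figure reproduces and this point does not touch it.

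**Inputs for ALI**
- 200 patients per arm (statistical considerations).
- π, the share with ALI at randomisation: not in the article; assumed 10% and 30%.
- New-onset risk without (i₀) and with (i₁) plasma: not in the article; assumed 5% v 15%, and 15% v 30%. The 30% borrows the upper figure that the Background gives for ALI in transfused ICU patients.
- Patients with ALI at randomisation are assumed still to meet the definition at 24 hours.

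**Formulas**
- Risk at 24 hours counting all cases: q = π + (1 − π) × i. The difference is therefore (1 − π)(i₁ − i₀).
- Power, two-sided 5%, unpooled normal approximation: Φ(d/SE − 1.96), with SE = √{[p₀(1 − p₀) + p₁(1 − p₁)]/n}.
- All cases: p = q, n = 200. New cases only: p = i, n = 200(1 − π).

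**One case in full (5% v 15%, π = 30%)**
- All cases: q₀ = 0.30 + 0.70 × 0.05 = 0.335; q₁ = 0.30 + 0.70 × 0.15 = 0.405; d = 0.07; SE = √[(0.2228 + 0.2410)/200] = 0.0482; power = Φ(1.454 − 1.96) = 31%.
- New cases only: n = 140; d = 0.10; SE = √[(0.0475 + 0.1275)/140] = 0.0354; power = Φ(2.828 − 1.96) = 81%.

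**Results**

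| New-onset risk | π | 24-hour risk, all cases | Relative risk: true, observed | Power, all cases | Power, new cases only |
|---|---|---|---|---|---|
| 5% v 15% | 10% | 14.5% v 23.5% | 3.0, 1.62 | 64% | 89% |
| 5% v 15% | 30% | 33.5% v 40.5% | 3.0, 1.21 | 31% | 81% |
| 15% v 30% | 10% | 23.5% v 37.0% | 2.0, 1.57 | 84% | 93% |
| 15% v 30% | 30% | 40.5% v 51.0% | 2.0, 1.26 | 56% | 86% |

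The direction is the same in every row. The size is not: the power lost is 9 percentage points in the third row (93 − 84) and 50 in the second (81 − 31).

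**The case against.** The strongest reply is that the article nowhere says existing ALI will be counted. Onset and development, in their plain sense, leave it out; any versus none describes a variable type shared with minor bleeding and serious adverse events; and a condensed article may leave the case rule to a full protocol or analysis plan that is not shown. Part of this stands: that only a 24-hour score exists is read from the absence of any other, and a fuller document may supply one. But the article does state a measurement time, a film time, an analysis variable and a set of tests, and carried out as stated these give ALI present at 24 hours.

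Four stronger readings are tempting and are not supported.
- *The design hides the plasma effect or biases the arms against each other.* Randomisation balances existing ALI in expectation. The effect is attenuated, not removed.
- *Most of the power is lost.* That depends wholly on assumed rates, as the table shows.
- *No change can be measured.* Respiratory and blood gas data are collected, and calling the later assessments repeated suggests an earlier one. The component with no stated pre-procedure measurement is the film.
- *The lung score is unblinded.* The article states blinding for the primary endpoint and the limited physical examination and does not say who reads the film. Within a design of blinded end point evaluation, that silence is article-level detail.

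It is also fair to say that ALI is one of several secondary outcomes and that the trial is sized only for bleeding.

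**Conclusion.** The point holds in limited form. The endpoint is named as new ALI, while the stated measurement and analysis yield ALI present at 24 hours, including cases that preceded randomisation. The consequence is attenuation toward no difference and lost precision in a secondary comparison. The non-inferiority conclusion on bleeding is untouched.

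The direction needs only that some patients have ALI at entry and still have it at 24 hours. The size rests on prevalence and incidence that the article does not give, so the table is an illustration and not an estimate for this trial. The change is worth making because it is inexpensive and because a later analysis plan can redefine the variable but cannot recover baseline information that was never captured. The article reports recruitment as still under way, so capture was still possible.

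**What to change.** 1. Derive a Lung Injury Score before randomisation from the respiratory and blood gas data and the latest available routine chest film.
2. State the cut-off that defines ALI, and define the binary outcome as ALI at 24 hours among patients below that same cut-off at baseline. Baseline status precedes allocation, so this remains a randomised comparison.
3. Compare the 24-hour score between arms with adjustment for the baseline score, instead of by an unadjusted test.
4. Where there is no baseline film, compute both the baseline and the 24-hour score from the same non-radiographic components, and report this as a sensitivity analysis. A baseline score without a film is not comparable with a 24-hour score that includes one.

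The cost is one derived baseline variable and a few lines of analysis text. The onset analysis uses fewer patients (for example 140 per arm instead of 200 if 30% have ALI at entry), and some baseline films will be missing. No extra radiograph or reader is required.
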